**Methods:**

Participants (*n* = 120, aged 60–75 years) will be randomly allocated into five groups: 1-Control (CON), 2-Supervised exercise without motivational intervention (SUP), 3- Supervised exercise with motivational intervention (SUP +), 4- Unsupervised exercise without motivational intervention (UNSUP) and 5- Unsupervised exercise with motivational intervention (UNSUP +). Over 24 weeks, all exercise groups will participate in a multicomponent exercise program three times/week (performed in group classes at a center for SUP and SUP + , or home without supervision but with the help of a mobile app for UNSUP and UNSUP +), while the CON group will maintain their usual lifestyle. The motivational intervention (for SUP + and UNSUP + groups) will be based on the self-determination theory, including strategies such as phone calls, interactive workshops, motivational messages, informative infographics and videos. Primary outcomes will include safety, adherence, costs, and lower-body muscular function using a leg press machine. Secondary outcomes will include upper-body muscular function, physical and cardiorespiratory function, blood pressure and heart rate, body composition, health-related quality of life, cognitive performance, anxiety, depression, physical activity levels, sleep and sedentarism, biochemical markers, motivators and barriers to exercise. Assessments will be conducted at baseline, mid-intervention (*i.e.,* week 13), at the end of the intervention (*i.e.,* week 25), and 24 weeks later (*i.e.,* week 49).

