### Outcome measures

#### Primary outcomes

##### Safety

The number of falls and adverse events will be recorded. Participants in the CON, UNSUP, and UNSUP + groups will record their falls and adverse events during and outside exercise sessions with a diary [39, 40]. In the SUP and SUP + groups, the sports scientist will register the incidence of falls and adverse events during exercise sessions, and participants will register them outside the exercise sessions using a diary.

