### Statistical analysis

Data will be preferentially presented as mean ± standard deviation or as proportions for continuous and categorical variables, respectively. Data normality will be assessed by the Kolmogorov–Smirnov test and will be log-transformed in case of non-normal distribution. Baseline differences will be assessed through a one-way ANOVA. A two-way mixed ANCOVA (group [*i.e.*, CON, SUP, SUP + , UNSUP, and UNSUP +] x time [*i.e.,* baseline, mid, post-intervention, and follow-up assessments]) will be performed, adjusting for baseline values as well as for any other sociodemographic/descriptive variables that may differ between groups (*e.g.,* age, sex). Subsequent post-hoc tests will be conducted to determine which groups significantly differ. Effect sizes will be calculated to assess the magnitude of the differences [87]. Falls and fall-related injuries will be presented as rates/person (ITT analysis) and rates/person/year (± 30 days; PP analysis), and as numbers. Adverse events and dropouts will be compared between groups through Chi-squared tests. Differences in adherence rates will be analyzed using an ANOVA test. Correlation analyses will be used to assess associations between motivators, barriers, and adherence to exercise sessions. Whenever possible, statistical analyses will be performed on an intention-to-treat (ITT) basis (including all randomized participants). The potential effects of missing values and dropouts will also be explored using multiple imputation and sensitivity analyses [88]. As recommended, a complementary per protocol (PP) analysis will be performed (*i.e.,* including only those participants with valid data for baseline and post-intervention assessments and an adherence to exercise program of at least 80%) [89]. SPSS version 24.0 (IBM Corp., Armonk, NY) will be used for statistical analysis, and the significance level will be set at p ≤ 0.05 for all tests.

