## Discussion

The main objective of the present trial is to examine the role of supervision and motivational strategies on the safety, adherence, efficacy, and cost-effectiveness of 4 different exercise programs for improving physical and mental health among people between 60 and 75 years old. We hypothesize that all exercise programs will be safe, and those that add cognitive-behavioral and motivational strategies will result in greater adherence and efficacy. Furthermore, we expect that UNSUP + will be the most cost-effective option, thereby increasing the accessibility of exercise to all older adults and consequently improving their health and quality of life.

As recommended by the World Health Organization, older adults should perform 150–300 min/week of moderate-intensity aerobic physical activity, 75–150 min/week of vigorous-intensity aerobic physical activity, or a combination thereof, as well as multicomponent physical activity focusing on functional balance and resistance training (≥ 3 days per week) [90]. The benefits of multicomponent exercise for mental and physical health are widely known [91–94]. Regular exercise helps in the prevention and management of different chronic diseases (*e.g.*, diabetes, obesity or overweight, hypertension, osteoporosis, or osteopenia) [95–98], thus leading to reduced attendance to medical consultations. According to Santos et al. [99], the global cost of inaction on physical inactivity would cost healthcare systems approximately 47.6 billion $ per year. If we add to this the low participation of older adults in physical activity, which decreases with age, we justify the need for safe and effective exercise programs for this population [16, 100].

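### No planned fall rate is both based on all randomised participants and adjusted for time at risk, and no between-arm contrast or interval is stated for falls, part of the primary safety outcome.

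*Protocol article*

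**What the plan says.** The abstract makes safety a primary outcome: "Primary outcomes will include safety, adherence, costs, and lower-body muscular function using a leg press machine". The Safety subsection under Primary outcomes gives it two components: "The number of falls and adverse events will be recorded". The Discussion adds a hypothesis: "We hypothesize that all exercise programs will be safe".

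The Statistical analysis section then fixes how falls are handled: "Falls and fall-related injuries will be presented as rates/person (ITT analysis"). The same sentence goes on to plan a rate per person-year (± 30 days) for the per-protocol analysis, and raw numbers. The next sentence treats the other safety component differently: "Adverse events and dropouts will be compared between groups through Chi-squared tests".

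The same section defines the two sets. Where possible, "statistical analyses will be performed on an intention-to-treat (ITT) basis (including all randomized participants"). The per-protocol set requires valid baseline and post-intervention data and "an adherence to exercise program of at least 80" percent.

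**The concern.** Two features of the stated handling cause difficulty.

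First, the denominators are matched to the analysis sets in an unhelpful way. Dropout occurs in the set of all randomised participants, and there the rate is falls per person: someone who leaves early counts as a full person but contributes little recording time. The per-protocol rate uses time, but that set is selected after randomisation. It leaves out people who stopped or attended less, possibly because of a fall. Controls have no exercise programme, so the adherence threshold has no meaning for them and membership of the set is undefined for the comparator.

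Second, falls are presented while adverse events and dropouts are compared. The trial's aim includes the effect of supervision and motivation on safety. Few falls are likely, because people with three or more falls in the past year are excluded. Bare rates on few events give the reader no means of separating chance from a real difference, in either direction. A statement that the programmes are safe would then rest on figures with no stated precision.

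**Working it through.** The documents give no fall rate, so there is no planned figure for falls to reproduce; the sample size was set on lower-body muscle power.

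**Inputs from the protocol article:** 120 participants, five arms, a 24-week intervention, 20% expected dropout, assessments to week 49.

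**Assumptions:** equal allocation, so 120/5 = 24 per arm (the ratio is not stated); true rates of 0.2, 0.4 or 0.6 falls per person-year, equal in all arms; Poisson counts; fall recording for 24 or for 48 weeks (the duration is not stated).

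**Step 1: which fall rates exist.**

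| Stated rate | All randomised? | Uses time at risk? |
|---|---|---|
| Per person, ITT | yes | no |
| Per person-year, per-protocol | no | yes |

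Neither rate meets both conditions.

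**Step 2: effect of the missing denominator.** If a fraction d of an arm leaves at mid-period, mean exposure is 1 − d/2 of full follow-up. With equal true rates, falls per person are proportional to exposure.
- 10% against 30% dropout: (1 − 0.05)/(1 − 0.15) = 0.95/0.85 = 1.12. The arm losing 30% shows the lower rate.
- None against 20%: the ratio is 0.90 if dropout is at mid-period and 0.80 if it is at the start.

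**Step 3: chance differences and precision for pooled supervised (48) against pooled unsupervised (48).** Person-years per pooled group are 48 × 24/52 = 22.15, or 48 × 48/52 = 44.31. Expected falls μ are the person-years times the rate. The chance of a crude ratio of two or more in either direction is the exact probability for two independent Poisson counts with mean μ (one group with no falls and the other with at least one counts as twofold). The 95% interval factor each way is exp(1.96 × √(2/μ)).

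| Weeks | Rate | μ per group | Chance of a twofold ratio or more | Interval factor |
|---|---|---|---|---|
| 24 | 0.2 | 4.43 | 41% | 3.73 |
| 24 | 0.4 | 8.86 | 20% | 2.54 |
| 24 | 0.6 | 13.29 | 11% | 2.14 |
| 48 | 0.2 | 8.86 | 20% | 2.54 |
| 48 | 0.4 | 17.72 | 6% | 1.93 |
| 48 | 0.6 | 26.58 | 2% | 1.71 |

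Example for the first row: √(2/4.43) = 0.672; 1.96 × 0.672 = 1.317; exp(1.317) = 3.73. Falls clustering within individuals would widen the intervals.

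**The case against.** The strongest reply is that presenting rates describes a reporting format. It does not forbid intervals or a contrast, and a journal article may leave a count model to an analysis plan that is not shown. This has weight: the absence of a model alone would not be a finding, and a reader should not infer that the plan rules out any comparison of falls. What stands is that the article positively assigns a denominator to each analysis set and names tests for the neighbouring outcomes.

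A reader might also infer that no person-time rate is planned at all. That is wrong: the same sentence plans one, but only in the per-protocol set.

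Dropouts will be compared between arms, and missing data explored by multiple imputation and sensitivity analyses. Differential dropout would thus be visible, but the stated ITT fall rate would still lack time.

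It is tempting to point to the spread across all five arms. Over 24 weeks with equal true rates of 0.2 to 0.8, the highest arm is at least twice the lowest in 97 to 67% of trials. The documents plan no comparison of highest with lowest, and at low rates the figure is inflated by arms with no falls, so it is not used here.

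Falls might be counted among adverse events and so reach the chi-squared test. The article lists them separately, and that test gives neither a rate ratio nor an interval. The sentence on effect sizes follows the ANCOVA and post-hoc tests and is not tied to falls.

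Finally, the imprecision comes from the trial's size, and no model removes it. That is true. It argues for showing the imprecision, not for testing falls.

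**Conclusion.** The point holds in this limited form. No stated fall rate both keeps all randomised participants and accounts for time at risk, and the stated handling of falls includes no contrast or measure of uncertainty.

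The denominator effect is modest, about 12% under the assumed dropout of 10% against 30%, but it favours the arm that loses more people. Random variation is much larger: the interval for the pooled rate ratio spans a factor of 2.1 to 3.7 each way over 24 weeks, or 1.7 to 2.5 over 48. These sizes depend on the assumed fall rates, equal allocation, recording period and dropout timing. The mismatch of denominators with analysis sets does not. This should be changed; it does not threaten the trial as a whole.

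**What to change.** For all randomised participants, report falls and fall-related injuries per person-year of observed follow-up. Define follow-up as time under fall recording by diary or session record, because in the supervised arms the sports scientist records falls during sessions and the diary covers only those outside.

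Give rate ratios with 95% intervals from a Poisson model with log follow-up time as offset and robust standard errors, or from a negative binomial model if its dispersion can be estimated. Use exact intervals where an arm has zero or very few falls: at 0.2 per person-year over 24 weeks, an arm of 24 expects 2.2 falls and has none in about 11% of trials (exp(−2.2) ≈ 0.11).

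Report pooled supervised against pooled unsupervised arms, and each exercise arm against control, beside the raw counts. Read them as estimation, since the trial was not sized for falls. State the recording period, and keep the per-protocol rate as supplementary, saying how controls enter that set.

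The cost is a small amount of extra analysis on data already planned, provided that each participant's recording time is kept. The intervals will be wide, and the safety statement will have to be more cautious.

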Although supervised center-based exercise interventions (herein referred to as supervised exercise for simplicity) are commonly prescribed to older adults, on some occasions feasibility can be limited by economic constraints, convenience, and access or time commitments [17, 18]. Under this context, unsupervised home-based exercise programs (herein referred to as unsupervised exercise) emerge as a potential alternative, and indeed different meta-analyses have shown that, compared with no exercise, unsupervised exercise can be effective for improving components of health and fitness in older adults [19, 20]. However, to date, there is no consensus on whether unsupervised exercise programs can be as effective –or even more cost-effective– than supervised ones. Some studies have shown greater benefits on different health variables with professionally supervised exercise programs compared to those performed autonomously at home [21–23]. On the other hand, other studies indicate that unsupervised exercise programs can be as effective as supervised ones [24–26]. For instance, Fisher et al. [27] found that supervised resistance exercise induces slightly greater muscle strength gains compared to unsupervised exercise in teenagers and adults, with minimal to no extra benefits on body composition. If their safety and cost-effectiveness are confirmed, unsupervised exercise programs would represent an alternative for increasing the accessibility of exercise for older adults, which would be of relevance for future public health policies. Nonetheless, most studies comparing supervised and unsupervised exercise have applied different interventions in each group (*e.g.,* different training types, duration, intensity, and exercise selection) [21]. Additionally, groups are often labeled as ‘supervised’ despite including some unsupervised sessions, and vice versa [28]. Therefore, well-designed randomized controlled trials (RCTs) that equalize exercise dose (*i.e.,* type, frequency, intensity, and volume) between both groups are warranted to draw definite conclusions on the role of supervision on the effectiveness of exercise programs.

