### Study design

The study will follow a single-blind randomized, parallel design. Participants will be randomized into 5 groups (Fig. 2): 1- Control group (CON), 2- Supervised exercise without motivational intervention (SUP), 3- Supervised exercise with motivational intervention (SUP +), 4- Unsupervised exercise without motivational intervention (UNSUP) and 5- Unsupervised exercise with motivational intervention (UNSUP +). Assessments will be conducted at baseline (week 0), mid-intervention (week 13), at the end of the intervention period (week 25), and 24 weeks later (week 49).

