### Sample size

The sample size was determined by a priori power analysis using G ∗ Power 3.1.9.4 software. Input parameters were entered considering repeated measures ANOVA (group by time interaction), setting the probability of α error at 0.05, 1-β = 0.80, and 5 groups. The standardized mean difference used for calculations was 0.43, based on the effect of home-based exercise on lower-body muscle power in older adults reported in a previous meta-analysis [19]. The model indicated a total sample size of 100 individuals, and considering a dropout rate of 20%, we finally decided to enroll 120 participants.

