### Randomization and blinding

The randomization will be performed by a researcher not involved in the study. The allocation sequence will be determined by a computer-generated list (http://www.randomizer.org/). If a couple living in the same house participates, both will be randomized into the same group [37]. Blinding of the intervention is impossible for participants and therapists administering the intervention given its nature (*i.e*., exercise training). During the intervention, subjects will not be told about the existence of groups with and without motivational strategies. Statisticians and assessors in charge of outcome assessments will be blinded to participants’ allocation.

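### The only test named for adverse events, a chi-squared test of difference with about 24 participants per arm, cannot establish the stated hypothesis that all exercise programmes are safe, and no interval or criterion for safety accompanies it

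*Protocol article*

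**What the plan says.** The abstract puts safety among the primary outcomes: "Primary outcomes will include safety, adherence, costs, and lower-body muscular function using a leg press machine". The Safety section defines what is collected: "The number of falls and adverse events will be recorded". The Discussion attaches a hypothesis to it: "We hypothesize that all exercise programs will be safe". No threshold, margin or other criterion for calling a programme safe is given. The Background explains why the answer matters: "If their safety and cost-effectiveness are confirmed, unsupervised exercise programs would represent an alternative".

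Statistical analysis names one inferential method for adverse events: "Adverse events and dropouts will be compared between groups through Chi-squared tests", with the significance level for all tests set at 0.05. Falls and fall-related injuries are treated separately, as rates per person, rates per person-year and counts, with no test named. The same section says that categorical variables will generally be shown as proportions and that effect sizes will be calculated. It mentions no confidence interval.

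On size, the Sample size section ends with "we finally decided to enroll 120 participants", and Study design says "Participants will be randomized into 5 groups". The calculation behind the 120 concerns lower-body muscle power, not safety.

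**The concern.** The hypothesis and the test point in different directions. The hypothesis asserts that something is absent or small: the programmes carry no unacceptable risk. A chi-squared test takes equality of the groups as its null. If it rejects, there is evidence that risks differ. If it does not, little has been learned unless the test had good power against differences that matter. Nor does equality between arms amount to safety, since all arms could share a high risk.

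What is at stake is the reading of a primary outcome. If adverse events are uncommon, the likeliest result in arms this small is a non-significant p-value, and that could be read as supporting the hypothesis in the Discussion. An interval would show how much risk the data leave open; a p-value does not.

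**Working it through.** **Inputs from the article.** 120 enrolled, five arms, significance level 0.05. The article gives the allocation method ("The allocation sequence will be determined by a computer-generated list") but no ratio, so equal allocation is an assumption: 120 / 5 = 24 per arm. With the planned 20% dropout, 120 / 1.2 = 100 and 100 / 5 = 20 per arm.

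**The plan's own figure.** There is none for safety. The stated 100 for muscle power can be reproduced (98, or 100 in equal arms) with f = 0.43 / 2 = 0.215, five groups, four measurements and a correlation of 0. The effect size conversion and the correlation are assumptions. Then 100 × 1.2 = 120. Nothing in this calculation bears on adverse events.

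**Inputs assumed.** The article gives no adverse-event risks, so a range is shown. The outcome is taken as whether a participant has at least one adverse event.

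**Power of the five-group test.** Pearson chi-squared, 4 degrees of freedom, critical value at 0.05, simulated binomial counts, 24 per arm. CON, SUP and SUP+ have the lower risk; UNSUP and UNSUP+ have the higher risk.

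| Risk in CON, SUP, SUP+ | Risk in UNSUP, UNSUP+ | Power |
|---|---|---|
| 5% | 10% | 8% |
| 10% | 20% | 19% |
| 5% | 15% | 25% |
| 20% | 40% | 44% |
| 30% | 60% | 75% |

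If only one arm has a raised risk, power is 39% for 5% against 20%, 15% for 10% against 20%, and 46% for 10% against 30%.

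If the true risk is 5% in every arm, the expected count is 24 × 0.05 = 1.2 participants with an event per arm, and the test rejects in about 2.6% of trials instead of the nominal 5%. It is therefore conservative when events are rare.

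**What zero events would exclude.** The two-sided exact 95% upper limit with 0 events in n participants is 1 − 0.025^(1/n).

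- One arm, n = 24: 1 − 0.025^(1/24) = 14.2%. The one-sided limit, 1 − 0.05^(1/24), is 11.7%.
- One arm after dropout, n = 20: 1 − 0.025^(1/20) = 16.8%.
- Two arms pooled, n = 48: 1 − 0.025^(1/48) = 7.4%.
- All four exercise arms, n = 96: 1 − 0.025^(1/96) = 3.8%.

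Each limit bounds the per-person risk of a kind of event that was not seen in the participants counted. The pooled limits are much tighter, and the pooled supervised and unsupervised groups are the ones that the question about supervision compares.

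**The case against.** A reader might infer that the trial will treat a non-significant chi-squared result as proof of safety. The documents do not support that. Statistical analysis says only that groups will be compared, the Discussion names no test or decision rule, and nothing links the two. The Background sentence about confirmed safety describes what the field needs; it is not a rule for this trial.

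The comparison is also legitimate in itself. Whether adverse-event risk differs between groups is part of the stated aim of finding the effect of supervision and motivation on safety. The plan does not rely on testing alone either: falls, the other half of the safety outcome, are reported as rates and counts, and proportions and effect sizes are foreseen. Interval methods and pooled summaries often sit in a full protocol or analysis plan, which is not at hand. Finally, low power depends on the assumed risk. Diaries cover events inside and outside sessions, so adverse events may be common, and at 30% against 60% power is 75%.

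Most of this stands and limits the point. What it does not remove is the mismatch within the article itself: a hypothesis of safety is stated for a primary outcome, the one inferential method named for adverse events cannot confirm it, and no criterion for safety is given. Details in an unseen plan could supplement the test but would not make it suit that hypothesis.

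**Conclusion.** The point holds in a limited form. The chi-squared test is not wrong as a comparison of groups, but it cannot establish that the programmes are safe. At 24 per arm its power runs from about 8% to 44% for increases from base risks of 5% to 20% in both unsupervised arms, reaching 75% only when events are very common. Zero events in one arm would still leave a risk of up to 14.2% open (16.8% with 20 participants), or 3.8% across all four exercise arms. These figures rest on equal allocation and, for power, on assumed event risks.

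That non-significance could be mistaken for safety is a risk the wording leaves open, not something the plan commits to. Severity is minor to moderate.

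**What to change.** Keep the chi-squared test and add the following to Statistical analysis:

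- The proportion of participants with at least one adverse event, with an exact 95% confidence interval, for each arm, for the two supervised arms pooled, for the two unsupervised arms pooled, and for all exercise arms.
- Risk differences with 95% confidence intervals for supervised against unsupervised and for exercise against CON.
- Confidence intervals for the fall rates already planned.
- A sentence that a non-significant test is not evidence of safety, and that any statement about safety will quote the upper confidence limit.

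The safety hypothesis in the Discussion should be worded to match. No extra data or participants are needed. The cost is a more modest safety claim.
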